### **9.8.2 Premature termination of the study**

The sponsor reserves the right to discontinue the study for safety, ethical, or administrative reasons. Should the study be discontinued, no further vaccinations will be administered but volunteers who are still actively participating at the time of discontinuation will be followed through the remainder of their follow up visits.

### **9.8.3 Study pausing rules**

If the trial is placed on safety pause, all enrollment and vaccinations will be suspended pending review. The AEs that may lead to a safety pause or prompt PSRT AE review are summarized below in Table 2. These AEs apply both to volunteers and household contacts. Vaccinations may be suspended for safety concerns other than those described in the table, or before pause rules are met, if, in the judgment of the PI or PSRT, volunteer or household contact safety may be threatened.

**Table 2: AE notification and safety pause/AE review rules**

| Event and relationship to study product                                                                                      | Severity                  | Occurrence          | Site PI action                                               | PSRT or SMC action                                   |
|------------------------------------------------------------------------------------------------------------------------------|---------------------------|---------------------|--------------------------------------------------------------|------------------------------------------------------|
| SAE, related                                                                                                     | Any                       | Any                 | Phone, email or fax forms to sponsor within 24 hours         | Study pause within 24 hours, refer to SMC for review |
| SAE, not related                                                                                                 | Grade 5                   | Any                 | Phone, email or fax forms to sponsor within 24 hours         | PSRT review within 2 business days to consider pause |
| AE  , related                                                                                        | Grade 3 or 4  | Second  | Phone, email or fax notification to sponsor within 24 hours  | Study pause within 24 hours, refer to SMC for review |
| AE  , related                                                                                        | Grade 3 or 4  | First               | Phone, email or fax notification to sponsor within 24 hours  | PSRT review within 2 business days to consider pause |
| Documented VISR in household contact                                                                                         | N/A                       | Any                 | Phone, e-mail or fax notification to sponsor within 24 hours | Study pause within 24 hours, refer to SMC for review |
| Documented illness compatible with Ad26 infection associated with a positive Ad26 serology in household contact  | N/A                       | Any                 | Phone, email or fax forms to sponsor within 24 hours         | Study pause within 24 hours, refer to SMC for review |

 Related SAE refers to SAE deemed to be definitely, probably, or possibly related to study vaccine.

 Not related SAE refers to SAE deemed to be probably not related or not related to the study vaccine.

 Does not include the following reactogenicity symptoms (fatigue/malaise, myalgia, arthralgia, chills, headache, nausea, vomiting).

 Related AE refers to fever, conjunctivitis, gastroenteritis, cystitis, upper respiratory infection, or other AE that is judged probably or definitely related to the vaccine.

 If no evidence of disease is present other than an abnormal laboratory value, the test must be repeated (entailing blood re-draw) at least one time. The verification period will be a maximum of 72 hours after initial awareness of the abnormal laboratory value. When signs and symptoms are present, repeat test will not be needed.

 PSRT will determine whether the reported related AE (Grade 3 or 4) is a second occurrence of a previously reported AE (Grade 3 or 4).

 "Positive Ad26 serology" means a \*newly\* positive Ad26 serology compared to enrollment that develops \*after\* a documented illness compatible with Ad26 infection in a household contact.

For events in the table above, the Site Principal Investigator (PI) notifies the IAVI Medical Monitor (within a few hours after the site observes, or is notified of, the AE) and the IAVI Medical Monitor then notifies the PSRT immediately (within 24 hours). The PSRT will convene within two business days to review these AEs. The PSRT will review and determine disposition (including whether the SMC needs to review the event).

If a study pause is triggered, all enrollment and vaccinations will be held until review by the SMC. Resumption of enrollment and study treatment may be determined by the SMC (in consultation with the FDA, if required) following a cumulative review of the available safety data. If a decision to resume study enrollment and study treatment

administration is made, the SMC will record its judgment in a memorandum to the study file and notify the sponsor, who will then forward the memorandum to the principal investigators. The clinical site will be allowed to resume activities upon receipt of written notification from the sponsor or its designee. As needed, the appropriate regulatory authorities will be informed in writing of the decision by the SMC to resume or discontinue study activities. The site is responsible for notifying their IRBs according to local standards and regulations. The sponsor is responsible for notifying the FDA.

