### **7.3 Household Contact Inclusion Criteria**

Household contacts must be deemed eligible according to the following criteria, before the volunteer is vaccinated:

1. Able to understand and give written consent, and complete an assessment of understanding
2. Healthy (based on medical history and physical examination) men or women aged 18-60.
3. Low risk for HIV infection (see Section 18.2) and willing to maintain low-risk behavior for 4 months following the volunteer's vaccination
4. Willing to undergo HIV testing and receive HIV test results and as well as risk-reduction counseling
5. Willing to forgo blood or tissue donation for 4 months after the volunteer's vaccination; for those who test HIV positive due to trial vaccination (vaccine-induced HIV seropositivity), until the anti-HIV antibody titers become undetectable
6. If a woman of child-bearing potential, committed to use an effective method of contraception when sexually active with men for 4 months following the volunteer's receipt of vaccine, including:
  - a. Condoms (male or female) with or without spermicide

- b. Diaphragm or cervical cap with spermicide
  - c. Intrauterine device
  - d. Hormonal contraception
  - e. Successful vasectomy in the male partner (considered successful if a woman reports that a male partner has [1] documentation of azoospermia by microscopy, or [2] a vasectomy more than 2 years ago with no resultant pregnancy despite sexual activity post-vasectomy)
  - f. Not be of reproductive potential, such as having undergone hysterectomy, bilateral oophorectomy, or tubal ligation
7. All sexually active males (unless anatomically sterile) must be willing to use an effective method of contraception (such as consistent condom use) from the conclusion of the isolation period until at least 4 months after vaccination

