#### **7.4 Household Contact Exclusion Criteria**

1. Significant acute or chronic disease, including inflammatory bowel disease or other chronic gastrointestinal disease, immunodeficiency syndrome, or condition requiring immunosuppressant medications (the use of topical or inhaled steroids is permitted)
2. Asthma other than mild to moderate, well-controlled asthma. Exclude a volunteer who:
  - Generally uses a bronchodilator (beta 2 agonist) daily, or
  - In the past year has (any of the following):
    - Had > 1 exacerbation of symptoms treated with oral steroids
    - Routinely used high dose inhaled corticosteroids (e.g., more than the equivalent of 500 mcg fluticasone; 1200 mcg budesonide; 500 mcg beclomethasone; or 1000 mcg triamcinolone/flunisolide, as a daily dose) or theophylline
    - Needed hospitalization, or intubation for asthma
  - Prophylactic bronchodilator use prior to exercise is not exclusionary
3. Pregnant or lactating
4. HIV infection
5. Individuals employed as a healthcare worker with direct patient contact, childcare worker who has direct contact with children <5 years old, or food handler (or an individual who is otherwise engaged in the preparation or delivery of food outside of their place of residence)

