A suspected transmission of any infectious agent via a medicinal product is always considered as an important medical event, i.e. an SAE.

Although **not** considered as an SAE, cancer should be reported in the same way as SAEs.

Note: If anything untoward is reported during an elective procedure, that occurrence must be reported as an AE, either serious or non-serious according to the criteria defined above.

When in doubt as to whether hospitalization occurred or was necessary, the AE should be considered serious.

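### Table 2's pause rule for a compatible illness with positive Ad26 serology cannot be triggered by a household contact who was already Ad26-seropositive at enrolment

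*Protocol*

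**What the plan says.** The last row of Table 2 in Section 9.8.3 reads "Documented illness compatible with Ad26 infection associated with a positive Ad26 serology in household contact". Any single occurrence pauses the study within 24 hours and refers it to the Safety Monitoring Committee (SMC). Footnote 7 defines the serology as a newly "positive Ad26 serology compared to enrollment that develops" after the illness, with the words for newly and after marked for emphasis. It gives no alternative based on a titre rise, PCR or culture.

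Section 7.3 states that "Household contacts must be deemed eligible according to the following criteria, before the volunteer is vaccinated" and lists seven criteria. Section 7.4 lists five exclusions. None of the twelve concerns Ad26 serostatus. Section 18.6 schedules Ad26 serology for contacts at screening and on Days 28, 112 and 240.

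Other routes to a pause also cover contacts, because Section 9.8.3 applies Table 2 to them:

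- "Documented VISR in household contact" at any occurrence.
- A related SAE of any severity. Footnote 1: "Related SAE refers to SAE deemed to be definitely, probably, or possibly related to study vaccine". Section 10.1.1 adds: "A suspected transmission of any infectious agent via a medicinal product is always considered as an important medical event", that is, an SAE.
- A related Grade 3 or 4 AE: review by the Protocol Safety Review Team (PSRT) at the first, a pause at the second.
- Suspension if the PI or PSRT judges that "volunteer or household contact safety may be threatened".

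**The concern.** The row is the one automatic trigger in Table 2 that ties a contact's illness to laboratory evidence of Ad26 infection, whatever the severity of the illness. It works by seroconversion. A contact who already has Ad26 antibody can be infected by the vector, fall ill and show a large titre rise, yet still be classed as positive before and positive after. The row is then silent.

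The vector is replication competent. The planned escalation review uses data through Day 9 for the group just dosed. Those volunteers are in isolation until then, so their contacts at home have not yet been exposed. Section 6 adds that shedding data will not be available to that review. Evidence of spread to a contact therefore has to reach the dosing decision later, through Table 2 or through judgment. A rule that drops out for an identifiable subgroup weakens that protection.

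**Working it through.** The protocol computes no figure on this point. The check is a reading of the rule followed by a count of the contacts for whom it is inactive.

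**Step 1: can the row fire?** Take two contacts with the same Grade 1-2 compatible illness, no VISR, and a rise in Ad26 antibody afterwards.

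| | Seronegative at enrolment | Seropositive at enrolment |
|---|---|---|
| Illness plus serology row | Fires: newly positive | Cannot fire: not newly positive |
| VISR row | No VISR, does not fire | No VISR, does not fire |
| Related Grade 3-4 AE rows | Grade too low | Grade too low |
| Related SAE row | Fires if reported as suspected transmission | Fires if reported as suspected transmission |
| PI/PSRT discretion | Available | Available |

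Only the first line differs. For the seropositive contact a pause needs someone first to suspect transmission, and a result that simply stays positive gives no prompt to do so.

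**Step 2: can such contacts be enrolled?** Yes. No criterion in Sections 7.3 or 7.4 excludes them. The screening draw in Section 18.6 makes their status measurable, though the protocol does not say that the result is returned before enrolment.

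**Step 3: which contacts matter for dosing?** Each volunteer receives a single dose and group 4 is dosed last, so results from group 4 contacts cannot stop any later dosing. That leaves groups 1-3.

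**Step 4: how many?** Inputs:

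- 5 vaccinees per group (Table 1), so 3 × 5 = 15 in groups 1-3.
- 0 to 2 contacts per volunteer (Section 6.5), so at most 15 × 2 = 30.
- Seroprevalence p = 8% to 11% (Section 4.1; neutralizing antibody in a US survey).

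The expected number for whom the row is inactive is m × p. The chance of at least one is 1 − (1 − p)^m.

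| Contacts per vaccinee | m | Expected, p = 0.08 | Expected, p = 0.11 | At least one |
|---|---|---|---|---|
| 2 (maximum) | 30 | 30 × 0.08 = 2.4 | 30 × 0.11 = 3.3 | 1 − 0.92^30 = 92% to 1 − 0.89^30 = 97% |
| 1 | 15 | 15 × 0.08 = 1.2 | 15 × 0.11 = 1.65 | 1 − 0.92^15 = 71% to 1 − 0.89^15 = 83% |
| 0 (all live alone) | 0 | 0 | 0 | 0 |

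**Step 5: what would a fourfold-rise criterion cost in false alarms?** A fourfold rise is 2 on the log2 scale. With no true change, and two readings each with standard deviation s, P(false rise) = P(Z > 2/(√2 × s)).

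- s = 0.5 (assumed): P(Z > 2.83) = 0.0023.
- s = 0.7 (assumed): P(Z > 2.02) = 0.0217.

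Because of blinding, placebo households would be tested too, so the ceiling is 24 × 2 = 48 contacts at three follow-up visits. That gives 48 × 0.08 × 3 × 0.0023 = 0.03 to 48 × 0.11 × 3 × 0.0217 = 0.34 false rises over the whole study, before requiring an illness, which lowers it further.

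**The case against.** The strongest reply is that Section 10.1.1 already closes the gap. Read literally, suspected transmission of any infectious agent through a medicinal product is always an SAE. Table 2 applies to contacts, and a related SAE, even if only possibly related, pauses the study at any severity and on first occurrence. That route acts on suspicion, before serology, and ignores baseline antibody. In addition, Section 6.5 brings a contact with a suspect illness to clinic, where PCR and culture may be done, and direct detection does not depend on serostatus. Footnote 7's emphasis also shows a deliberate choice: old antibody should not halt the trial.

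Much of this stands. The SAE clause is a strong backstop, and requiring a new result has a sound purpose. A reader might infer that vector spread to a seropositive contact could never pause the study; the documents do not support that, since four other routes remain. What survives is that the SAE route needs someone to suspect transmission, the swabs in Section 6.5 are optional and no part of the row, Section 9.6.1 regards VISR in contacts as unlikely, and the Grade 3-4 rows miss mild and moderate illness. Protecting against old antibody does not require ignoring a rise in titre.

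A reader might also take the number of seropositive contacts as the number of missed pauses. It is not. A missed pause also needs transmission, a compatible illness and no other route firing, and the protocol gives no basis for that probability. Pre-existing immunity may lower it, but the documents do not say by how much.

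**Conclusion.** The point holds in a narrow form and is minor. On the plain wording, this row of Table 2 cannot be triggered by a contact seropositive at enrolment, and such contacts are eligible. The consequence is confined to a mild or moderate illness without VISR that nobody reports as a suspected-transmission SAE or acts on at discretion.

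The size is a ceiling, reached only if every vaccinee in groups 1-3 has two contacts. It assumes that the Section 4.1 survey range applies to these contacts and to their assay, whose type and cut-off the protocol does not state. Counting the contacts of all 20 vaccinees would give a larger number, but it would include group 4. How soon the scheduled serology arrives affects seronegative contacts equally and is not part of this point.

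**What to change.** Keep the newly-positive criterion in footnote 7 and add an alternative: in a contact seropositive at enrolment, a prespecified rise in Ad26 titre over the enrolment sample (for example at least fourfold, paired samples tested in the same run), developing after a documented compatible illness. The row's action stays as it is, and antibody that merely persists still triggers nothing. The fourfold threshold is a proposal and does not come from the protocol; the laboratory should confirm it against its own assay variability.

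The sera are already scheduled in Sections 18.6 and 18.8, so there is no extra visit or draw. Three practical conditions must be added, because the protocol states none of them for contacts: the screening serum is retained, the assay yields a titre, and the pair is run together. The remaining downside is the small risk of a false rise calculated above.

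### Section 9.8.3 words PSRT discretion over SMC review to cover every Table 2 event, against the four pause-and-refer rows, and lets the pause for a second related Grade 3 or 4 event wait on a PSRT step allowed two business days

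*Protocol*

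**What the plan says.** Table 2 (Section 9.8.3) has six rows. Four carry the action "Study pause within 24 hours, refer to SMC for review": a related SAE, a second related Grade 3 or 4 AE, vaccine-induced seroreactivity in a household contact, and Ad26-compatible illness with new Ad26 seropositivity in a household contact. The other two, an unrelated Grade 5 SAE and a first related Grade 3 or 4 AE, carry "PSRT review within 2 business days to consider pause".

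The paragraph below the footnotes covers every event in the table. The site tells the Medical Monitor "within a few hours after the site observes, or is notified of, the AE"; "the IAVI Medical Monitor then notifies the PSRT immediately (within 24 hours"); the PSRT is to meet within two business days. It then says: "The PSRT will review and determine disposition (including whether the SMC needs to review the event").

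Footnote 6 governs the second-occurrence row: "PSRT will determine whether the reported related AE (Grade 3 or 4) is a second occurrence" of one already reported. Footnote 5 allows an abnormality seen only in a laboratory value to be confirmed first: "The verification period will be a maximum of 72 hours after initial awareness of the abnormal laboratory value".

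Section 10.9 gives the PSRT a choice about SMC review only for AEs that do not require a pause. Section 9.5 makes a pause follow whenever a Table 2 criterion is met. The next paragraph of Section 9.8.3 holds enrollment and vaccination until the SMC has reviewed.

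**The concern.** This is the pausing rule of a first-in-human trial of a replicating vector. The SMC is the independent body and may see unblinded data. The PSRT is made up of protocol chairs, investigators and the sponsor's Medical Monitor. Two features of the rule do not fit together.

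First, the sentence on disposition has no exception for the rows that order a pause and referral. Taken alone, it makes optional what the table makes mandatory.

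Second, the second-occurrence row promises a pause within 24 hours, but whether an event belongs in that row is for the PSRT to decide, and the PSRT's only related time limit is longer than 24 hours. A repeat related Grade 3 or 4 event could leave vaccination unpaused for several days with every stated deadline met.

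**Working it through.** **Scope.** Each row's action set beside the disposition sentence and Section 10.9:

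| Table 2 row | Action in the table | PSRT choice over SMC review under 10.9 | Disposition sentence fits? |
|---|---|---|---|
| Related SAE | Pause, refer to SMC | No | No |
| Unrelated SAE, Grade 5 | PSRT considers pause | Yes | Yes |
| Related Grade 3/4 AE, second | Pause, refer to SMC | No | No |
| Related Grade 3/4 AE, first | PSRT considers pause | Yes | Yes |
| Household seroreactivity | Pause, refer to SMC | No | No |
| Household Ad26 illness with new seropositivity | Pause, refer to SMC | No | No |

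The sentence is contradicted in 4 of 6 rows and fits 2 of 6. Even in those two it is incomplete: if the PSRT elects to pause, the next paragraph requires SMC review.

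**Timing of the second-occurrence row.** Inputs from Section 9.8.3: Medical Monitor to PSRT, at most 24 hours; PSRT meeting, within two business days; pause, within 24 hours.

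Assumptions, none stated in the Protocol: the two business days run from notice to the PSRT, the footnote 6 decision is made at that meeting, and there are no holidays. Day 0 is notification to the Medical Monitor; the few hours from site to Medical Monitor are not counted.

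Latest decision day = day the PSRT is told + two business days, in calendar days:

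| Medical Monitor told on | PSRT told same day | PSRT told at 24 hours |
|---|---|---|
| Monday | 2 | 3 |
| Tuesday | 2 | 3 |
| Wednesday | 2 | 5 |
| Thursday | 4 | 5 |
| Friday | 4 | 4 |
| Saturday | 3 | 3 |
| Sunday | 2 | 3 |
| Range | 2-4 | 3-5 |

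The decision may thus come 2-5 days after notification. If the 24 hours to pause start only at the decision, add 1 day: 2 + 1 = 3 to 5 + 1 = 6, so the pause may come 3-6 days after notification. If the 24 hours instead start at notification, the pause is due by day 1, before the latest permitted decision (day 2 at the earliest). One reading gives a delay; the other lets the limit lapse before the step it depends on.

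**Exposure.** A group is 6 volunteers, 5 on vaccine. They are planned to enter isolation together (Section 9.8.4), and the next group waits for SMC review of D0-D9 (Section 10.9). AEs are collected to Day 112 (Section 10.1.2.2) and all four groups are expected to enroll within 6 months (Section 6), so an event after Day 9 in an earlier group can still arise shortly before Day 0 of Group 2, 3 or 4, each at a ten-fold higher dose than the group before.

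**The case against.** The strongest reply is that the document already resolves the scope question. The four table rows, Section 9.5, Section 10.9 and the hold until SMC review all point the same way. That stands. A reader might infer that the PSRT can keep a pause-row event from the SMC, but the sections read together do not allow it. What remains is a sentence that contradicts the rule it explains.

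On timing, the 24 hours sit in the column for PSRT or SMC action, apart from the site's own duty ("Phone, email or fax notification to sponsor within 24 hours"), so the natural reading is that the site reports and the committee then acts. That also stands. A reader might conclude that all four pause rows can overrun because no clock start is given. For the three rows with no recurrence decision this is mostly missing detail.

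Nor is the footnote 6 decision without any date: the meeting limit bears on it. The PSRT could also decide before it meets, and the PI or PSRT may suspend vaccination before a rule is met. These points make a long delay unlikely, but neither obliges anyone to act within 24 hours.

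One could add up to 3 days of laboratory verification and quote 6 + 3 = 9 days. That would mislead: verification is deliberate, applies only to laboratory-only findings, and should stay.

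Finally, with a single dose and joint entry, there is usually no vaccination left to stop in the group already dosed. This limits the size of the point without removing it. The SMC charter is not shown, but it would not correct the Protocol text that the site and the PSRT follow.

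**Conclusion.** The point holds in two limited parts. The disposition sentence is wrongly scoped: it contradicts 4 of 6 Table 2 rows and Section 10.9, although the intended rule is clear. The second-occurrence pause depends on a PSRT decision that may come 2-5 calendar days after the Medical Monitor is told, with the pause at 3-6 days if its clock starts only then.

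The day counts rest on the assumptions listed above and are permitted outer limits, not expected delays. They have a consequence only when the event falls shortly before a later group's Day 0 and nobody uses the discretionary suspension. Minor to moderate; worth correcting because it is a stated safety rule and the correction is short.

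**What to change.** Two edits to Section 9.8.3:

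1. Limit the disposition sentence to the two rows that do not require a pause (unrelated Grade 5 SAE; first related Grade 3 or 4 AE). State that every other Table 2 event, and any event for which the PSRT elects to pause, goes to the SMC.
2. Add to footnote 6 that when a related Grade 3 or 4 AE may be a recurrence of one already reported (after footnote 5 verification where that applies), the Medical Monitor provisionally pauses enrollment and vaccination within 24 hours of being told. The pause lasts until the PSRT decides; if the event is not a second occurrence, it is handled as a first.

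The second edit covers possible recurrences only, because a pause for any further related Grade 3 or 4 event would be a different and broader rule. It brings the limit from 3-6 days to 1 day after notification to the Medical Monitor. The clock start for the other three pause rows can be stated in the same amendment, as a clarification.

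The cost is one amendment with no added data or volunteers. The downside is an occasional short pause that proves unnecessary and could delay a group's Day 0.
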